## Abstract

**Background:**

Tobacco dependence management is a multi-component intervention that includes pharmacological treatments such as Nicotine Substitution Therapy (NST) or bupropion, and psychological therapy. There are some preliminary reports on topiramate efficacy for tobacco dependence. The aim of this study is to determine whether topiramate is as effective as the standard NST treatment for tobacco cessation at 1-year follow-up in patients with depression.

**Method/design:**

*Design: *A randomised, controlled trial involving two groups, one of which is the control group consisting of patients on the standard pharmacological treatment for tobacco cessation (NST) and the other is the intervention group consisting of patients on topiramate as pharmacological treatment.

*Setting: *29 primary care health centres in the city of Zaragoza, Spain.

*Sample: *180 patients, aged 18–65 years, diagnosed with major depression, smoke more than 20 cigarettes/day, who have voluntarily asked for tobacco cessation therapy.

*Intervention: *A multi-component programme for tobacco cessation is offered to all of the patients in the study. This programme is made up of pharmacological therapy + group cognitive-behavioural therapy. Pharmacological therapy consists of NST for the control group and topiramate (200 mg/day) for the intervention group. Psychological therapy is made up of 16 sessions of manualised group therapy.

*Measurements: *Cessation will be assessed by patient self-declared abstinence, expired air carbon monoxide levels, and cotinine levels in saliva. Questionnaires on tobacco dependence, anxiety, depression, impulsiveness and self-efficacy will be administered. The interviewers will not know which group the patient belongs to (blind). The assessments will be carried out at baseline, D (cessation day) -1, D+1, weeks 1, 2, 3, 4, 6, 8, 10 and 13, and months 4, 5, 6, 8, 10 and 12.

*Main variables: *Tobacco cessation rates and tobacco dependence.

*Analysis: *The analysis will be per intent to treat. We will use the general linear models of the SPSS version 15 statistical package, to analyse the effect of the treatment on the result variable (tobacco cessation rate).

**Discussion:**

It is necessary to develop new and more effective pharmacological treatments for tobacco cessation. This randomised clinical trial will determine whether topiramate is effective for tobacco cessation in patients with depression.

**Trial registration:**

Current Controlled Trials ISRCTN93532081

## Background

Tobacco abuse is the main avoidable cause of death and disability in the world that is unrelated to others. The World Health Organization (WHO) estimates that 4 million persons died of tobacco-related disorders in 2002 [1]. In Spain, the latest available data from the National Health Survey (Encuesta Nacional de Salud) in 2003 [2] describe a prevalence of tobacco consumption of 31%, with a decrease in consumption by males, and a small but significant increase in consumption by females, mainly in adolescents and young women. For these reasons tobacco use is considered a public health problem and its treatment constitutes a challenge for health services.

At present, tobacco dependence management is carried out in a collaborative way in primary care and specialised settings by means of treatments that range from minimal to intensive intervention [3]. In the latter, a multi-component cessation intervention is applied by health professional specialised in tobacco dependence management [4,5]. The multi-component intervention includes first-line pharmacological treatments for tobacco such as Nicotine Substitution Therapy (NST) or bupropion, and psychological treatments. This intervention obtains a remission rate of 30–40% at 1-year follow-up [5,6]. As psychological therapy, cognitive-behavioural interventions, which can be administered on a group or individual basis, are used with follow-up sessions during the first year of abstinence. NST is administered by transdermal patches as basal treatment [7-9], added to nicotine lozenges [10] or nicotine chewing gums [11] that are self-administered occasionally depending on abstinence symptoms. Bupropion is a noradrenergic and dopaminergic antidepressant used for tobacco dependence because it acts on nicotinic receptors. It is twice as effective as a placebo for this treatment [12]. However, in psychiatric patients it should be used with caution owing to potential interactions with CYP2D6, an enzyme involved in the metabolisation of many psychiatric drugs [13].

Topiramate seems to be a new and promising pharmacological treatment for tobacco. A new antiepileptic drug, it was originally designed as an oral hypoglycaemic, and was subsequently approved as an anticonvulsant. It has increasingly been used in the treatment of numerous psychiatric conditions (binge eating disorders, bulimia nervosa, and alcohol dependence) and it has also been associated with weight loss, potentially relevant in reversing weight gain induced by psychotropic medications [14]. Topiramate has demonstrated its efficacy for the treatment of alcohol dependence in randomised controlled trials [15]. There are also some preliminary reports of its effectiveness for the treatment of tobacco dependence, despite these reports being substudies of other trials on alcohol dependence [16], uncontrolled studies with small samples [17] or short-term studies [18].

Recently, a group of smokers have been described as "special populations". These are groups with certain characteristics that require the need for more intensive treatments to attain tobacco cessation, owing to limitations in the use of pharmacological treatments (pregnancy) or because the cessation must be more immediate (patients with heart disorders or emphysema) [4]. One of these special populations is psychiatric patients in whom prevalence of tobacco dependence is higher than in the general population (52% vs. 31%) and effectiveness of cessation programmes are less effective [19]. In persons who smoke, there is a direct relationship between severity of psychiatric symptoms and tobacco dependence [20]. Specifically, patients with depression show more likelihood to become heavy smokers, to have more difficulties in stopping smoking, and to suffer from more abstinence symptoms than general population [21]. At present, there are not enough research studies on the effectiveness of topiramate for tobacco cessation and, specifically, in psychiatric populations such as patients with depression.

## Methods/Design

### Objectives

The general aim is to determine whether topiramate is at least as effective as NST in tobacco cessation at 1-year follow-up in patients with depression. The specific aims are to determine the factors that predict a good response to topiramate treatment and the possible differences in effectiveness in relation to gender.

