### Statistical methods

#### Sample size

To calculate the sample size we consider the tobacco cessation rate at 1 year follow-up as the main outcome variable. On the basis of published research data [5,6], we assume that this will be 35% in the control (NST) group, and we aim to detect a difference of 25% or more between any of the two groups (control and intervention). Published studies place placebo response at 10% [32]. Accepting an alpha risk of 0.05 and a beta risk of < 0.20 in a bilateral contrast, we would need 90 patients in each group [33].

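### The aim is to show topiramate is no worse than NST, but the trial is sized as a two-sided test for a 25-point difference and states no margin, so a non-significant result would leave the aim unanswered

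*Protocol article*

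**What the plan says.** The Objectives section gives the general aim: to "determine whether topiramate is at least as effective as NST in tobacco cessation at 1-year follow-up". The Background paragraph of the Abstract words it as parity: to "determine whether topiramate is as effective as the standard NST treatment for tobacco cessation".

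The Sample size section frames the trial differently. The outcome is one-year cessation ("we consider the tobacco cessation rate at 1 year follow-up as the main outcome variable"). For the control rate, "we assume that this will be 35% in the control (NST) group". For the effect, "we aim to detect a difference of 25% or more between any of the two groups (control and intervention". For the error rates, "Accepting an alpha risk of 0.05 and a beta risk of < 0.20 in a bilateral contrast". The result is 90 patients per group. The same paragraph notes a placebo response of 10%.

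The Analysis strategy section plans an intention-to-treat analysis, with general linear models for the treatment effect on cessation. It gives no sidedness, margin or confidence-bound criterion. The Discussion paragraph of the Abstract words the purpose a third way: whether topiramate works for cessation at all.

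**The concern.** A claim that one treatment is at least as good as another needs a stated largest acceptable loss, and a confidence interval that excludes it. A two-sided test of no difference does not supply this. Failing to reject equality is compatible with real inferiority, especially in a trial of moderate size.

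This is not a detail left to an analysis plan. The article itself fixes the hypothesis on which the sample size rests, and it differs from the hypothesis in the Objectives. The mismatch concerns the primary aim and the outcome used to size the trial. If the result is neither clearly better nor clearly worse, the trial will have no stated basis for answering the question it was set up to answer.

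**Working it through.** **Inputs from the Sample size section:** control rate 35%; difference 25 points; alpha 0.05 two-sided; beta below 0.20; 90 per group. **Assumptions of this review:** equal true rates for the precision and non-inferiority figures; one-sided 2.5% for non-inferiority, which corresponds to a two-sided 95% interval; and an uncorrected pooled chi-squared test for the difference test, because the article names only a general linear model for cessation.

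**1. The plan's own figure.** With p̄ the mean of the two rates, n per group = [1.96·√(2p̄(1−p̄)) + z_β·√(p₁(1−p₁)+p₂(1−p₂))]² / 0.25².

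- 35% v 60%, 80% power: (1.96·0.706 + 0.842·0.684)² / 0.0625 = 61.4, so 62 (70 with continuity correction).
- 35% v 10%, 80% power: 42.6, so 43 (51 with correction).
- 35% v 60%, 90% power with correction: 90. This is compatible with beta below 0.20, but the 90% is not stated.
- A relative 25% would need 435 to 511 per group, so only an absolute difference fits.

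The stated 90 therefore fits a test of difference at more than 80% power. It also equals the non-inferiority size for a 20-point margin (step 3), but the article names no such margin.

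**2. Precision with 90 per arm.** SE = √(2·p·(1−p)/90).

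| True rate, both arms | SE | 95% CI half-width (1.96·SE) | Smallest margin with 80% power (2.802·SE) |
|---|---|---|---|
| 35% | 7.1 points | 13.9 points | 19.9 points |
| 20% | 6.0 points | 11.7 points | 16.7 points |

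The 20% row is an assumed lower rate, shown because the Discussion expects poorer cessation in psychiatric patients.

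**3. Non-inferiority at 35% in both arms.** Power at 90 per arm = Φ(margin/0.0711 − 1.96). Size for 80% power = 2·0.2275·(2.802/margin)².

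| Assumed margin | Power at 90 per arm | n per arm for 80% power |
|---|---|---|
| 10 points | 29% | 358 |
| 12.5 points | 42% | 229 |
| 15 points | 56% | 159 |
| 20 points | 80% | 90 |

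None of these margins is in the article. They show the range.

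**4. How often real inferiority would be non-significant.** Exact binomial enumeration, 90 per arm, NST at 35%:

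- topiramate truly 25%: non-significant in 69% of trials;
- topiramate truly 20%: non-significant in 38% of trials.

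**5. One possible result.** 32/90 v 21/90 is 35.6% v 23.3%. The pooled chi-squared test gives p = 0.07 and the 95% interval for topiramate minus NST is −25.4 to +1.0 points. That result is non-significant, yet compatible with a loss of 25 points.

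**The case against.** **The aim may be loosely worded superiority.** The article's discussions speak of a need for better drugs than those available, and a test of difference suits that. This is plausible, and if so the repair is only wording. But parity is the question in both the Abstract and the Objectives, so as written the aim and the test do not match.

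**The trial is not uninformative.** A reader might infer that it cannot answer its aim at all. That goes too far. A significant benefit would establish the aim and a significant deficit would refute it. With 90 per arm, approximate power is 93% for 35% v 60% and 98% for 35% v 10%. Only the outcome in between is unresolved.

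**The article never says how a non-significant result will be read.** A reader might infer that it will be reported as equivalence. No sentence says so. What stands is that no other criterion for concluding comparable effectiveness is given.

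**The 25 points might be taken as the whole NST effect.** It equals 35% minus the 10% in "Published studies place placebo response at 10"%, so it is tempting to treat it as the full benefit of NST and halve it for a margin. The article does not support this. Its Background describes the 30–40% rate as that of a multi-component programme of drug plus psychological therapy, and the setting of the placebo figure is not given. Here both arms also receive group therapy and free nicotine gum or lozenges. Nor does the article offer 25 points as a margin.

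**Drop-out need not favour similarity.** A reader might infer that it always does. If missing patients were counted as smokers (the article is silent), unequal drop-out could instead create a difference.

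**Conclusion.** The point holds. The stated aim is a non-inferiority or equivalence question, the trial is sized for a two-sided difference, and nothing links the two. At 35% in both arms, margins below about 20 points have under 80% power; at 20% in both arms the limit is about 17 points. A true 10-point deficit from 35% would be non-significant in about 69% of trials.

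The size of the problem depends on the assumed true rates and on the assumed chi-squared test. The mismatch itself depends on neither. That the stated 90 exceeds what 80% power literally requires is a separate matter and does not affect this conclusion.

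**What to change.** 1. In the Abstract and the Objectives, state the primary hypothesis as the two-sided comparison of one-year cessation that the Sample size section plans.
2. Add that a non-significant difference will not be reported as showing topiramate to be as effective as NST.
3. Report the risk difference with its 95% confidence interval as the main result.
4. If a non-inferiority statement is still wanted, fix and justify a margin before results are known, judge it by the confidence bound, and state the power that 90 per arm gives for it (29%, 42%, 56% or 80% for margins of 10, 12.5, 15 or 20 points at 35% in both arms). Do not derive the margin from 35% minus 10% without evidence that this is the NST effect on top of group therapy.

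**Cost:** items 1 to 3 change wording and reporting only and need no extra patients. Item 4 makes the stated power less favourable at any margin below about 20 points; reaching 80% power there would need the larger samples tabulated above.

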### Design

This is a controlled trial with a random allocation of patients into two alternative branches (see Figure 1):

**Figure 1 F1:**
[figure not shown]
Flowchart: randomisation, sampling and monitoring of patients.

1. Tobacco cessation standard treatment with NST (control group) and

2. Tobacco cessation treatment with topiramate (intervention group).

The evaluation of the treatment outcomes will be performed at patient level and they will be assessed individually.

### Setting and study sample

Patients will be recruited from any of the 29 primary health care centres in the city of Zaragoza (Aragonese Health Service), Spain. Patients will be recruited by doctors working in these primary care centres until the required sample is completed, without a quota of patients assigned for every centre.

Patients considered for **inclusion **are those aged 18–65 years, able to understand and read Spanish, who fulfil criteria for major depression (DSM-IV criteria), with scores on the Zung Self-Rating Depression Scale < 60 [22] (implying minimal to mild depression), who smoke more than 20 cigarettes/day, fulfil preparation state of change according to Prochaska & DiClemente [23], voluntarily ask for a tobacco cessation therapy, and sign informed consent. Those **excluded **will be patients with active psychosis and/or treatment with antipsychotic drugs, alcohol or drug abuse, and pregnancy or lactation.

### Randomisation, allocation and masking of study groups

Each patient will be allocated to either the intervention or the control group using a computer-generated random number sequence. The allocation will be carried out by an independent person, belonging to REDIAPP (Research Network on Preventative Activities and Health Promotion), who is not involved in the study. The method used to implement the random allocation sequence will be a central telephone. The sequence will be concealed until interventions are assigned. Patients agree to participate before the random allocation and without knowing which treatment they will be allocated to. Pharmacological treatment will be administered by a psychiatrist ([name]). Study personnel conducting psychological intervention and assessments ([name]) will be masked to participants' treatment conditions.

### Intervention

#### Psychological intervention in both groups

A multi-component programme for tobacco cessation is offered to all of the patients in the study. This is made up of pharmacological therapy + group cognitive-behavioural therapy. The group is made up of 7–12 patients with depression and tobacco dependence, and is led by 2 therapists (a psychologist and a family doctor) trained in group therapy and tobacco cessation. Each session lasts 90 min., and the structure of every session and the contents are manualised and based on the standard programmes of this type [19]. It consists of 16 follow-up sessions: D (cessation day) -1, D +1, weeks 1, 2, 3, 4, 6, 8, 10 and 13, and months 4, 5, 6, 8, 10 and 12. Patients will be offered a phone number on which study personnel can solve problems and answer queries in relation to psychological ([name]) or pharmacological treatment ([name]).

#### Pharmacological intervention

##### Intervention group

In this group of patients, topiramate at doses used for the treatment of addictions (100–200 mg/day) will be administered [15-17].

##### Control group (standard treatment)

In this group, NST (nicotine patches) at usual doses (21 mg/day first and second fortnight, 14 mg/day third fortnight and 7 mg/day fourth and last fortnight), will be offered.

Pharmacological treatments will be financed by the grant. It will be administered by a psychiatrist ([name]). Duration of treatment, in both groups, will be 8 weeks. All patients will have free use of nicotine gums or lozenges during the two months of the treatment.

### Measurements

The study personnel that carried out the measurements ([name]) will be unaware of which pharmacological treatment the patients is being administered ("blind"). The follow-up assessments will take place at baseline (clinical interview), D -1, D + 1, weeks 1, 2, 3, 4, 6, 8, 10 and 13, and months 4, 5, 6, 8, 10 and 12.

#### Variables and instruments of measurement (See Table 1)

**Table 1 T1:** Study variables

**Instrument**	**Assessment area**	**Applied by**	**Time(s) of assessments**
Sampling form	Age, sex, inclusion/exclusion criteria	Family doctor	Baseline
Sociodemographic data form	Age, sex, marital status, educational level, Socio-economic group (28), occupation	Research assistant	Baseline
MINI psychiatric interview, depression and tobacco dependence modules (27)	Psychiatric diagnosis	Research psychiatrist	Baseline
Zung Self-Rating Depression Scale (22)	Severity of depression	Research assistant	Baseline and possible relapses
State of change (23)	State of change	Research assistant	Baseline
Self-declared abstinence	Tobacco abstinence	Research assistant	Baseline and all follow-up sessions*
Minnesota tobacco abstinence symptoms (24)	Tobacco abstinence	Research assistant	Baseline and all follow-up sessions*
Expired air carbon monoxide levels (25)	Tobacco abstinence	Research assistant	Baseline and all follow-up sessions*
Cotinine levels in saliva	Tobacco abstinence	Research assistant	Baseline and all follow-up sessions*
Fagerström test for Nicotine Dependence (29)	Tobacco dependence	Research assistant	Baseline and many follow-up sessions**
State-Trait Anxiety Inventory (STAI) (30)	Anxiety	Research assistant	Baseline and many follow-up sessions**
Plutchik Impulsivity Scale (31)	Impulsivity	Research assistant	Baseline and many follow-up sessions**
Visual analog scale	Efficacy self-perception	Research assistant	Baseline and many follow-up sessions**
Medical record	Pharmacological side-effect events	Research assistant	Baseline and many follow-up sessions**

*All follow-up sessions: D (cessation day) -1, D + 1, weeks 1, 2, 3, 4, 6, 8, 10 and 13, and months 4, 5, 6, 8, 10 and 12 (16 sessions in total) **Many follow-up sessions: weeks 1, 4, 8 and months 4, 6, 8, 10, 12.

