##### Main outcome variables

In accordance with the aims of the study, the major outcome is tobacco cessation in patients with depression. The diagnosis of tobacco dependence will be made with the Spanish version of the MINI psychiatric interview substance dependence module adapted to tobacco [24]. This modification has been validated on a Spanish population with adequate psychometric properties [19]. Tobacco abstinence will be diagnosed by self-declared abstinence, self-administered Minnesota tobacco abstinence symptoms [25], expired air carbon monoxide [26], and cotinine in saliva. Tobacco abstinence, according to majoritarily-accepted criteria [27], has been defined using 2 concepts: 1. Occasional abstinence: In a follow-up visit, patients affirm that they have been abstinent, their levels of expired air carbon monoxide < 10 ppm, and cotinine levels in saliva < 5 ng/ml. Continuous abstinence: As of the visit at 30 days, patients affirm that they were abstinent the month before, expired air carbon monoxide levels < 10 ppm and cotinine levels in saliva < 5 ng/ml. Tobacco relapse will be diagnosed with the MINI psychiatric interview substance dependence module adapted to tobacco [24].

The diagnosis of depressive disorder will be made with the Spanish version of the MINI psychiatric interview, depression module [24], and the severity of the depression with the Spanish version of the Zung Self-Rating Depression Scale [22]. Recruitment will only include patients with depressive disorder and Zung scale scores < 60, which implies minimal to mild depression [22]. MINI psychiatric interview depression module [24], will be also used as criteria for depression relapse.

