#### Analysis strategy

The analysis will be per intent to treat. First we will compare the intervention group with the control group in order to verify that there are no significant differences between the two groups (socio-demographic characteristics, clinical baseline data, etc). We will use the mean (standard deviation) in the continuous variables and percentages in the categorical variables. For comparisons we will use the Student-t test for continuous variables and the Chi-squared test for categorical variables. Non-parametric tests may also be used.

The main variables of the result are the percentage of patients with tobacco cessation (patient's self-declared abstinence, expired air carbon monoxide levels, self-administered Minnesota tobacco abstinence symptoms, and cotinine levels in saliva), and tobacco dependence (Fagerström test for Nicotine Dependence scoring) at 1-year.

Process variables include severity of the depression (Zung Self-Rating Depression Scale), anxiety trait and state (STAI), impulsivity (Plutchik Impulsivity Scale), and efficacy self-perception (visual analogue scale).

We will use the general linear models of the SPSS 15 statistical package, to analyse the effect of the treatment on the categorical result variables (tobacco cessation rate). We will use the analyses of linear mixed models to analyse the effect of the continuous process variables (depression, anxiety, impulsivity and efficacy).

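### Zung depression scores are collected after baseline only at possible relapses, yet depression severity is to be analysed by linear mixed models alongside scales measured at eight fixed visits

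*Protocol article*

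**What the plan says.** Three places in the protocol article bear on this.

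- **Table 1 (Variables and instruments of measurement).** The Zung scale, given by the research assistant, is listed at "Baseline and possible relapses". STAI, the Plutchik scale and the self-efficacy visual analogue scale, given by the same person, are listed at baseline and at the sessions defined in the footnote: "Many follow-up sessions: weeks 1, 4, 8 and months 4, 6, 8, 10, 12". The MINI interview, given by the research psychiatrist, is listed at baseline only.
- **Analysis strategy.** "Process variables include severity of the depression (Zung Self-Rating Depression Scale), anxiety trait and state (STAI") and continue with impulsivity and self-efficacy. The plan is to use "linear mixed models to analyse the effect of the continuous process variables (depression, anxiety, impulsivity and efficacy").
- **Main outcome variables.** The section defines two kinds of relapse, tobacco and depression, each by a MINI module. The depression module "will be also used as criteria for depression relapse".

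No section gives the Zung scale a scheduled visit after baseline.

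**The concern.** The article states both a measurement schedule and a model for depression severity, and the two do not fit. Three of the four process variables in the mixed models have eight planned follow-up values per patient; depression severity has none. Its follow-up values arise only when a relapse is thought possible, so the follow-up data describe patients selected by an event that happens after randomisation and may be affected by treatment.

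At stake is the reading of depression over the year in a trial whose participants all have major depression. A treatment effect on mood would act mainly on who gets measured, while the scores of those who are measured would look alike in the two arms. Scores that were never taken cannot be recovered by a later analysis.

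**Working it through.** The documents give no figure for the depression analysis, so there is none to reproduce. The check has two parts.

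**1. Schedule against model**

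| Process variable | Scheduled follow-up values | Planned model |
|---|---|---|
| STAI | 3 (weeks) + 5 (months) = 8 | linear mixed model |
| Plutchik | 8 | linear mixed model |
| Self-efficacy scale | 8 | linear mixed model |
| Zung | 0; only at possible relapses | linear mixed model |

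With 90 patients per arm, full attendance gives 2 × 90 × 8 = 1,440 follow-up scores for each of the first three variables and no scheduled score for Zung.

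Table 1 does not say which relapse triggers the scale, so each reading has to be followed through.

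- *Depression relapse.* A score is missing because the current, unrecorded depression is low. Missingness depends on the missing value, so the missing-at-random condition behind a mixed model fails.
- *Smoking relapse.* Smoking status is recorded at all 16 sessions, so missingness could be explained by observed data. But no Zung score would exist at any visit without a possible relapse, so the data say nothing about depression in sustained abstainers, and any estimate for them is extrapolation. On the sample-size assumptions (35% cessation in control, a 25-point difference, here taken in favour of topiramate), non-abstinence at one year would be 100 - 35 = 65% against 100 - 60 = 40%. The pool from which scores could come would differ by arm.
- *Depression as a predictor.* The baseline score is available for everyone. A time-varying score would again exist only for selected patients.

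**2. Size under the depression-relapse reading**

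From the documents: 90 per arm, entry Zung below 60, eight visits. Assumed: mean 50, SD 10 (range 8 to 12), within-patient correlation 0.6 (0.4 to 0.8), a constant arm effect after baseline, and a score taken only when it reaches 60 (also 55), with or without trigger noise of SD 5. The model has a random intercept per patient:

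score = b0 + b1·post + b2·(post × arm) + patient effect + error,

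where b2 is the arm difference after baseline. Each simulated trial was fitted twice: with all eight visits, and with triggered scores only.

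| Scenario | True b2 | All visits: estimate, power | Triggered only: estimate, power |
|---|---|---|---|
| Base case (67 runs) | -5 | -4.9, 100% | -1.5, about 10% |
| Base case (72 runs) | -3 | -3.2, 97% | -1.0, about 6% |
| Range (40 runs each) | -5 | -4.8 to -4.9, 100% | -0.8 to -2.2, about 3% to 23% |
| Trigger noise SD 5 (40 runs) | -3 | -2.8, 93% | -1.4, about 13% |

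At a true -5, the share of the difference lost runs from 1 - 2.2/5 = 56% to 1 - 0.8/5 = 84%. In that base case 6.6% of visits yield a score, about 0.066 × 1,440 = 95 of 1,440. About 36% of control and 16% of intervention patients ever contribute one. Across all scenarios with an effect, 4% to 17% of visits yield a score.

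The runs are few. At 40 runs, a power of 22.5% has a standard error of √(0.225 × 0.775 / 40) = 0.066, so the powers are approximate.

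**The case against.** The strongest reply is that nothing central depends on this. The main outcome is cessation, the sample size rests on it alone, and no stated aim compares depression between arms. The Analysis strategy speaks of the effect *of* the process variables, and the Objectives seek predictors of response, so depression may be a predictor, and baseline Zung is scheduled for everyone. The trigger may be smoking relapse, in which case the missing-at-random argument is not plainly lost. How a suspected relapse leads to a repeat MINI is the kind of detail a condensed article leaves to the full protocol. The figures above rest on an assumed score threshold.

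Much of this stands, and it limits the point to a secondary analysis. It does not remove the mismatch: the article itself fixes both the schedule and the model, and under every reading the follow-up scores are selected.

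Four stronger readings are tempting and are not supported.

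- A reader might infer that the arm difference disappears. That follows only if relapsers in both arms are given the same score, which makes it true by construction; the mixed model shows attenuation, not zero.
- A reader might infer from the Abstract that depression follows the general visit list. The Abstract says "Questionnaires on tobacco dependence, anxiety, depression, impulsiveness and self-efficacy will be administered" and lists the visits separately. It is a collective statement, and Table 1 restricts several of those questionnaires to a subset of visits.
- A reader might infer that relapses go undetected. The article plans to use the MINI for depression relapse and patients attend 16 sessions; what is unclear is only when the MINI is repeated.
- A reader might infer that the cessation result is biased. Nothing here touches it.

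**Conclusion.** The point holds for depression severity as a process variable: a should-fix. As written, post-baseline Zung scores would come only from patients selected by a post-randomisation event, and the planned mixed model does not undo that selection. If depression relapse is the trigger, a true difference of -5 points would be estimated at about -0.8 to -2.2, with power of roughly 3% to 23% instead of about 100%. These sizes rest on the assumed distribution, correlation and trigger, not on figures in the documents. If smoking relapse is the trigger, no size is claimed; the defect is that sustained abstainers have no follow-up score. If depression is only a predictor, the baseline score is sound and a longitudinal one is not.

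**What to change.** In Table 1, schedule the Zung scale at the visits already used for STAI, Plutchik and the self-efficacy scale: weeks 1, 4, 8 and months 4, 6, 8, 10, 12. Use those scheduled scores in the mixed model and keep relapse-triggered scores out of it. The cost is one more short self-rated questionnaire at eight visits that patients already attend, given by the research assistant who already gives the other scales.

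If that is not adopted, limit Zung to its baseline value as a predictor and drop depression from the longitudinal mixed models. This needs no new data, but gives up any description of depression over time by arm.

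In either case, say in Table 1 which relapse is meant, and reconcile Table 1 with Main outcome variables on when the MINI depression module is repeated. Adding psychiatrist-applied MINI interviews at fixed visits would need extra resources and is not required to resolve this point.
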